### Study population and sample size

The study sample will consist of 640 RTRs found to be lacking sufficient vitamin D (25OHD <30 ng/ml) 12 to 48 months post-transplantation with 320 subjects in each study group. Inclusion and exclusion criteria are detailed in the Appendix. The sample size calculation was performed according to the following assumptions: The principal criteria will be the occurrence of one of the events of the composite endpoint including *de novo* DM, major cardiovascular events, *de novo* cancer, and patient death. Over a 2-year follow-up period, we estimate, according to previous reports in the literature, that the incidence of a first event of the composite endpoint will be around 22% in our population (6% for *de novo* T2DM [91, 92], 6% for major cardiovascular events [93–95], 7% for *de novo* cancers [15, 96], and 3% for patient death). This 22% global estimated incidence does not take into account the fact that some patients may experience several events of the composite endpoint during the follow-up period. According to the results of the numerous observational studies showing an inverse association between 25OHD concentrations and various clinical events and to the results of the few interventional trials showing effects of high-dose vitamin D supplementation on these events (detailed above),we estimate that the overall decrease in the incidence risk of a first event of the composite endpoint will be around 40% in the high-dose group compared with the low-dose group (33% decrease for *de novo* DM, 40% decrease for major cardiovascular events and 50% decrease for *de novo* cancer). Thus, to demonstrate the reduction in the incidence of a first event of the composite endpoint from 22% in the low-dose group to 13% in the high-dose group, with a 90% power and 5% α risk error, 582 RTRs (291 in each group) will be required. Taking into account that 10% of patients will not be evaluable, a total of 640 RTRs will be required. The inclusion of a total of 480 RTRs would allow us to test the same hypothesis with a power of 80%.

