### Randomization and blinding

If all inclusion and none of the exclusion criteria are met and informed consent has been obtained, each RTR will be included in the study and allocated a randomization number used for assignment to one of the two treatment arms. The randomization list will be computer-generated and created using nQuery Advisor software (v6.01). The randomization will be stratified by centres, and blocks of four will be used in order to facilitate treatment distribution by the central pharmacy. The size of the blocks will be unknown to the investigators. The two treatment regimens will be randomly allocated in a 1:1 ratio. The attribution arm will be given centrally by Cleanweb® software after the validation of inclusion criteria, and this software also allows entering trial data for each patient. Participants, investigators, and outcome assessors will be blinded to the allocated treatment. Blinding will be ensured by the use of investigational products that are identical in packaging, labelling, appearance, smell, and taste. Unblinding will occur only in cases of emergency or at the conclusion of the study. In most cases, discontinuation of the treatment should be sufficient without the need for unblinding. Access to the randomization list will be restricted to the pharmacist involved in the study and a research assistant.

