The two side effects caused by vitamin D_3_ that may occur are increase in serum calcium levels or in urinary calcium excretion. At serum calcium levels >2.85 mmol/l, serum phosphate levels >1.8 mmol/l or in cases of major increase in urinary calcium excretion (increase in fasting baseline urinary calcium/creatinine ratio ≥0.4 mmol/mmol in the absence of furosemide introduction), the aforementioned monthly vitamin D_3_ administration will be discontinued. If the biological abnormalities cited above persist after vitamin D_3_ re-introduction, cholecalciferol treatment will be halted. Cholecalciferol treatment will be immediately discontinued in cases of proven graft nephrolithiasis (except for uric acid calculi, whose composition has been proven by calculi analysis) or nephrocalcinosis, symptomatic hypercalcemia, or pregnancy occurrence. VITALE is an ITT study. Consequently, in cases of cholecalciferol discontinuation, patient follow-up will be maintained according to the study guidelines until the end of the 24 month follow-up period.

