#### Statistical analysis

The ITT analysis will involve data on all patients in each dose group. All patients who are lost to follow-up for any reason will be treated as failures at the time of last contact or at the time of an event that results in discontinuation, whichever occurs first. The per-protocol set will exclude from the full analysis the set non-compliant patients, patients who received less than 50% of the treatment, and patients who received concomitant administration of an excluded treatment.

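### The 10% non-evaluable allowance does not match an intention-to-treat analysis that keeps every patient and counts losses as failures, so 90% power at 640 is not supported

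*Protocol article*

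**What the plan says.** **Sizing.** The section Study population and sample size plans for a "reduction in the incidence of a first event of the composite endpoint from 22% in the low-dose group to 13% in the high-dose group" and states that "with a 90% power and 5% α risk error, 582 RTRs (291 in each group) will be required". It then adds one allowance: "Taking into account that 10% of patients will not be evaluable, a total of 640 RTRs will be required". It does not define evaluability, does not say whether the 5% is one-sided or two-sided, and gives no expected rate of loss or of stopping treatment.

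**Analysis.** The Statistical analysis section says "The ITT analysis will involve data on all patients in each dose group". It adds that anyone lost to follow-up, for whatever reason, is treated as a failure, generally dated at last contact. Only the per-protocol set drops patients. The primary comparison is a Cox model for the first composite event, accounting for centre.

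**Stopping treatment.** The Study intervention section calls the trial an intention-to-treat study and says that "in cases of cholecalciferol discontinuation, patient follow-up will be maintained according to the study guidelines", up to month 24.

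**The concern.** A head-count allowance is right for patients who contribute nothing to the primary analysis: replacing them restores the number analysed and leaves the contrast alone. Under the stated rules no patient is in that position. A lost patient stays in and adds a failure to whichever arm he is in. That raises both event rates and shrinks the difference between them. A patient who stops high-dose treatment stays in and may move the high-dose rate towards the low-dose rate. Neither reduces the number analysed; both weaken the contrast, and adding 10% to the head count is not designed to repair that.

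At stake is how the result will be read. The stated 90% describes an analysis of evaluable patients with an undiluted effect, not the planned primary analysis. A null result judged against 90% power would look more informative than it is.

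**Working it through.** **Inputs from the protocol article.** Two-year first-event rates are 22% and 13%; alpha is 5%, sidedness not stated; 582 patients (291 per arm) are inflated to 640 for 10% not evaluable. "The two treatment regimens will be randomly allocated in a 1:1 ratio", so 640 is 320 per arm.

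**The plan's own figure.** The inflation is 582 × 1.1 = 640.2. The 582 does not follow from 22% versus 13% with a two-sided 5% test at 90% power:
- pooled two-proportion formula: 373 per arm, 746 in total;
- unpooled formula: 739;
- Schoenfeld: 126 events / 0.175 = 720.

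One-sided 5% gives 608, 602 and 584-589 respectively. A two-sided unpooled calculation at 22% versus 12% gives 582.5, but 12% is not in the text. The basis of 582 is therefore not identifiable, and both sidedness cases are carried below.

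**Formulas for power at n = 320 per arm.**
- Two proportions: z = [(p1 − p2)√n − z_α√(2p̄(1 − p̄))] / √(p1(1 − p1) + p2(1 − p2)), with p̄ the mean of p1 and p2.
- Schoenfeld: z = (√D / 2)·|ln HR| − z_α, with D = n(p1 + p2) and HR = ln(1 − p2)/ln(1 − p1).

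Power is Φ(z), with z_α = 1.960 two-sided or 1.645 one-sided.

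**No loss, no stopping (22% versus 13%), two-sided.**
- Two proportions: (0.09 × 17.889 − 1.960 × 0.5374) / 0.5336 = 1.04, power 85.2%.
- Schoenfeld: D = 320 × 0.35 = 112, HR = 0.560, z = 5.292 × 0.579 − 1.960 = 1.10, power 86.5%.

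**Loss counted as failure.** With share f lost in each arm, independently of risk, each rate becomes (1 − f)p + f. At f = 10%:
- low dose: 0.9 × 22 + 10 = 29.8%; high dose: 0.9 × 13 + 10 = 21.7%;
- the difference falls from 9.0 to 8.1 points while both variances rise;
- D = 320 × 0.515 = 164.8, HR = 0.691, z = 6.419 × 0.369 − 1.960 = 0.41, power 65.9%.

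**Stopping treatment (assumption).** With share f of the high-dose arm losing all the effect, that arm's rate becomes (1 − f) × 13% + f × 22%. At f = 10% this is 11.7 + 2.2 = 13.9%. If those patients lose half the effect it is 13.45%, the same rate as 5% losing all of it.

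| Scenario | Low dose | High dose | Two-sided power | One-sided power |
|---|---|---|---|---|
| No loss, no stopping | 22% | 13% | 85.2-86.5% | 91.3-92.2% |
| 5% lost per arm, counted as failures | 25.9% | 17.35% | 74.9-76.0% | 83.8-84.6% |
| 10% lost per arm, counted as failures | 29.8% | 21.7% | 65.0-65.9% | 75.8-76.6% |
| 10% of high-dose arm stop, half the effect lost | 22% | 13.45% | 81.0-82.3% | 88.4-89.3% |
| 10% of high-dose arm stop, all the effect lost | 22% | 13.9% | 76.2-77.5% | 84.9-85.8% |
| 20% of high-dose arm stop, all the effect lost | 22% | 14.8% | 65.3-66.4% | 76.1-77.0% |

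Each range runs from the two-proportion to the Schoenfeld result.

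**Sensitivity to the basis of 582.** At 22% versus 12%, two-sided, 640 starts at 92.2-93.4%. It falls to 85.2-86.5% if 10% stop with full loss of effect, and to 74.6-75.6% if 10% per arm are lost and counted as failures. On the bases that give about 582, the extra 58 patients cover only about 2.5-5.5% of the high-dose arm losing the whole effect.

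**The case against.** The sample size section does not say that its 10% are patients off treatment. The ordinary meaning of not evaluable is a patient without usable endpoint data, and for such patients a head-count allowance is normal practice. Nor does the section say that 13% is an undiluted rate. The assumed reduction ("the overall decrease in the incidence risk of a first event of the composite endpoint will be around 40% in the high-dose group") draws on both observational studies and trials and may already allow for imperfect adherence. The plan also limits dilution: other vitamin D products are excluded, returned vials are checked, and treatment suspended for a laboratory abnormality may be re-introduced. An assumption that 10% of high-dose patients carry the low-dose risk from day 0 is therefore severe. With half the effect lost, one-sided power is 88-89%, close to the stated figure.

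Most of this stands, and it limits the point. A reader might infer that the plan's 10% are treatment stoppers and that dilution alone takes power from 90% to a particular lower value. The document does not support that. It gives no stopping rate and names no one-sided test, and on a two-sided test 640 already falls short at 22% versus 13% without any dilution.

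The objection does not rescue the allowance itself. Read as missing endpoint data, the 10% run straight into the rule that counts losses as failures. That rule leaves such patients in the analysis and costs more power than the same share of patients stopping treatment.

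**Conclusion.** The point holds in a limited form. The 10% allowance describes patients leaving the analysis, while the stated intention-to-treat rules keep them all, so 90% power at 640 is not supported for the planned primary analysis.

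The loss-as-failure result needs the fewest outside assumptions: it takes the plan's own 10% as losses, equal in both arms and unrelated to risk, and applies the plan's own counting rule. The stopping-treatment results rest on an assumed share and an assumed loss of effect, and they would double count if the 40% reduction already allows for non-adherence.

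Two limits apply. On a one-sided test with no loss and no stopping, 640 does exceed 90%. On a two-sided test, the shortfall before any loss is a separate fault in 582 and should not be attributed to dilution.

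**What to change.** In Study population and sample size:

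1. Define not evaluable so that it agrees with the loss-as-failure rule in Statistical analysis. If some patients really are to be left out of the primary analysis, say which.
2. State whether the 5% alpha is one-sided or two-sided.
3. Restate the power of 640 on intention-to-treat event rates that include expected loss, counted as the analysis section counts it, and expected stopping of treatment, for example at 5%, 10% and 20%. Put the 480-patient fallback on the same basis.
4. Say whether the 40% reduction already allows for non-adherence. If it does, omit the separate stopping term.

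Leave the enrolment target unchanged. The cost is one recalculated power statement. The downside is that the stated power becomes less favourable.

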### Study design and setting

The VITALE study is a prospective, multicentre, double-blind, randomized trial with two parallel groups. Patient recruitment, kidney transplants, postoperative care, and follow-up are currently conducted in 30 transplantation departments in France, and there are about 2,700 kidney transplantations performed each year in France. In the absence of vitamin D supplementation, approximately 80% of RTRs are expected to have insufficient vitamin D. Of these patients, 20% to 30% are expected to fulfil the inclusion criteria and to agree to participate in the study. Consequently, the recruitment phase will last approximately 2 years, with a follow-up period of 2 years for each subject. The flowchart of the VITALE study is shown in Figure 1.

**Figure 1 Fig1:**
[figure not shown]
**Flowchart of the VITALE study.** RTR with 25OHD insufficiency (25OHD <30 ng/ml) will be included 12 to 48 months after renal transplantation in 30 transplantation departments in France, and randomized to receive either high-dose cholecalciferol treatment (100,000 IU every other week, equivalent to 6,600 IU daily for 2 months, then 100,000 IU monthly, equivalent to 3,300 IU daily for 22 months) or low-dose cholecalciferol treatment (12,000 IU every other week, equivalent to 800 IU daily for 2 months, then 12,000 IU monthly, equivalent to 400 IU daily for 22 months, which is the French recommended dietary intake). Duration of patient follow-up will be 2 years. VITALE is a double-blind study as a single-dose vial of 100,000 or 12,000 IU have exactly the same appearance. We aim to include 320 RTR sin each group (high-dose group and low-dose group) over a period of approximately 2 years. Statistical analysis will be performed at the end of the study.

### Randomization and blinding

If all inclusion and none of the exclusion criteria are met and informed consent has been obtained, each RTR will be included in the study and allocated a randomization number used for assignment to one of the two treatment arms. The randomization list will be computer-generated and created using nQuery Advisor software (v6.01). The randomization will be stratified by centres, and blocks of four will be used in order to facilitate treatment distribution by the central pharmacy. The size of the blocks will be unknown to the investigators. The two treatment regimens will be randomly allocated in a 1:1 ratio. The attribution arm will be given centrally by Cleanweb® software after the validation of inclusion criteria, and this software also allows entering trial data for each patient. Participants, investigators, and outcome assessors will be blinded to the allocated treatment. Blinding will be ensured by the use of investigational products that are identical in packaging, labelling, appearance, smell, and taste. Unblinding will occur only in cases of emergency or at the conclusion of the study. In most cases, discontinuation of the treatment should be sufficient without the need for unblinding. Access to the randomization list will be restricted to the pharmacist involved in the study and a research assistant.

### Study intervention

At 12 to 48 months after renal transplantation, RTRs found to have 25OHD levels below 30 ng/ml and who fulfil all of the inclusion and none of the exclusion criteria will be randomized to receive either high-dose y (100,000 UI every 2 weeks for 2 months, then monthly for 22 months) or low-dose (12,000 UI every 2 weeks for 2 months, then monthly for 22 months) oral cholecalciferol therapy. With a total follow-up of 2 years. Each 2 ml vial will contain either cholecalciferol 100,000 IU or 12,000 IU plus butylhydroxytoluene 0.2 mg, saccharin 1.2 mg, sorbic acid 4.00 mg, lemon essential oil 6.0 mg, with glycosylated polyoxyethylenated glycerides making the quantity up to 2 ml. High-dose and low-dose vials will be produced by Crinex (Montrouge, France). It will be recommended that cholecalciferol be ingested concomitantly with a fatty meal to improve intestinal absorption of vitamin D_3_ [97]. The intensive phase of the high-dose arm was previously demonstrated to correct 25OHD insufficiency in RTRs [12], and the maintenance phase was demonstrated in a theoretical scheme to maintain 25OHD above 30 ng/ml after kidney transplantation [14]. The 12,000 IU cholecalciferol monthly dose during the 22 month-maintenance phase, equivalent to 400 IU daily, was chosen because it is in agreement with the French recommended dietary intake [98], and this dose has been proven to avoid severe vitamin D deficiency and osteomalacia [99]. To evaluate adherence to treatment, patients will be asked to return the treatment boxes containing the empty ampoules at each follow-up visit.

The two side effects caused by vitamin D_3_ that may occur are increase in serum calcium levels or in urinary calcium excretion. At serum calcium levels >2.85 mmol/l, serum phosphate levels >1.8 mmol/l or in cases of major increase in urinary calcium excretion (increase in fasting baseline urinary calcium/creatinine ratio ≥0.4 mmol/mmol in the absence of furosemide introduction), the aforementioned monthly vitamin D_3_ administration will be discontinued. If the biological abnormalities cited above persist after vitamin D_3_ re-introduction, cholecalciferol treatment will be halted. Cholecalciferol treatment will be immediately discontinued in cases of proven graft nephrolithiasis (except for uric acid calculi, whose composition has been proven by calculi analysis) or nephrocalcinosis, symptomatic hypercalcemia, or pregnancy occurrence. VITALE is an ITT study. Consequently, in cases of cholecalciferol discontinuation, patient follow-up will be maintained according to the study guidelines until the end of the 24 month follow-up period.

### Concomitant medication

Most RTRs are treated with an immunosuppressive therapy consisting of mycophenolate mofetil or sodicum mycophenolate, tacrolimus, or ciclosporin, with (in most cases) or without prednisone. Steroid boli, monoclonal antibodies, and polyclonal antibodies are administered to treat acute rejection episodes. Medications will be allowed during the study, with the exception of active or native vitamin D_2_, active or native D_3_, and multivitamin complexes likely to contain vitamin D. Drugs with anti-secretory and gastric-dressing properties will be allowed, but will have to be ingested at least 4 hours after cholecalciferol treatment.

### Study procedure

#### Inclusion visit

At 12 to 48 months after kidney transplantation, each RTR found to have 25OHD levels below 30 ng/ml during a routine visit will be given information about the VITALE study, its purpose, putative benefits, and possible risks, and will be invited to participate in the trial. All patients will be informed that the participation in that study is voluntary, and that they may refuse to participate or withdraw from the trial at any time without giving reasons and without loss of benefits. RTRs who do not agree to participate in the study will receive standard care. If the RTR agrees, they will sign a written informed consent form, and demographic, clinical, and biological baseline data will be collected. In addition, daily calcium intake will be evaluated by means of a questionnaire.

#### Randomization

During the week following the inclusion visit, RTRs who agree to participate in the study will be randomized to receive either oral high-dose vitamin D_3_ therapy or oral low-dose vitamin D_3_ therapy. The day of the randomization defines the first day of the study.

#### Patient follow-up

Five visits will be performed after randomization (Table 1). Vitamin D measurements after randomization will be centralized and performed at the end of the study. Given the absence of standardization and a reference method of vitamin D measurement when we submitted the VITALE trial to funders (early 2011), we planned to use the most referenced method (radioimmunoassay; Diasorin, Stillwater, MN, USA) [100]. Since then, a reference method has been accepted [101] and is now being used in an international program, the Vitamin D Standardization Program (VDSP), to harmonize vitamin D results [102]. We thus will use the assay (either immunoassay or commercial LC-MS-MS assay) that at the end of the VITALE study will provide results that are closest to the reference method [103]. This will allow us to determine with the best possible precision the optimal threshold of 25OHD level to prevent the occurrence of the clinical events constituting the principal criteria. In order to assess compliance, patients will be asked to return their empty vials at each follow-up visit.

**Table 1 Tab1:** **Study procedures**

Date	Patients selection	Inclusion visit		M1	M2	M3	M6	M12	M18	M24
Cholecalciferol (high versus low dose)			**R = T0** ^**1**^	**Intensive phase (2 months)**		**Maintenance phase (22 months)**				
Written informed consent/checking of the inclusion and exclusion criteria		X								
Medical history entry		X								
Clinical examination, blood pressure, body weight and height		X				X	X	X	X	X
Current treatment		X				X	X	X	X	X
Notification of events constituting the primary composite criteria and the secondary criteria						X	X	X	X	X
Checking of treatment compliance						X	X	X	X	X
Notification of tolerance and side effects^2^						X	X	X	X	X
β-human chorionic gonadotropin if relevant		X								
25OHD	< 30 ng/ml	X				X^1^		X^1^		X^1^
Serum calcium^2^	<2.7 mmol/l	X				X	X	X	X	X
Serum phosphate^2^	<1.5 mmol/l	X				X	X	X	X	X
Fasting urinary calcium^2^		X				X	X	X	X	X
Fasting urinary creatinine^2^		X				X	X	X	X	X
Serum creatinine	<250 μmol/l	X				X	X	X	X	X
MDRD estimated glomerular filtration rate		X				X	X	X	X	X
Urinary protein/creatinine ratio		X						X		X
Urinary microalbumin/creatinine ratio		X						X		X
Fasting glycaemia	< 7 mmol/l	X				X	X	X	X	X
HbA1C		X						X		X
Liver function tests		X								X
Lipid profile		X						X		X
Complete blood count		X						X		X
Serum parathyroid hormone		X						X		X
Bone mineral density		X								X
Echocardiography^2^		X						X		X
DNA collection^3^		X								
Serum collection^3^		X				X		X		X

Table legend: M1 (M2, 3…): month one (two, three…) after randomization; MDRD: Modification of the Diet in Renal Disease; R: randomization; T0: time zero corresponding to the randomization of the patient.

^1^R: randomization represents the time 0 (T0). Intensive phase: cholecalciferol 100,000 IU or 12,000 IU every two weeks for 2 months. Maintenance phase: cholecalciferol 100,000 IU or 12,000 IU monthly for 22 months.

^2^Safety data. Echocardiography results will have to notify valvular calcifications.

^3^Samples for which the dosage (25OHD) and/or conservation will be centralized.

